## J. Outcome measures

The primary outcome is the incidence of perioperative anxiety in patients from the day of surgery to 3 days after surgery after two sessions of tDCS intervention. Perioperative anxiety was measured using the Hospital Anxiety and Depression Scale-Anxiety (HADS-A) (**Appendix 1**). A HADS-A score of 8 or more is considered to be a patient experiencing anxiety. On the day before surgery, the researcher assesses the patient for anxiety in the ward treatment room (T0), followed by a second assessment of anxiety (T1) after the first tDCS intervention. On the day of surgery, the researcher conducted separate assessments before (T2) and after (T3) administering the second tDCS stimulus. Anxiety scores were assessed at two hours after surgery (T4), on the

---

first day after surgery (T5), the second day after surgery (T6), the third day after surgery (T7), and the third month after surgery (T8).

Secondary outcomes included anxiety scores (T1-T8), the incidence of postoperative delirium (POD, assessed by the Confusion Assessment Method [CAM] or Confusion Assessment Method intensive care unit [CAM-ICU] **[Appendix 2]** on the day of surgery and three days after surgery [T4-T7]); pain scores (assessed by the Numeric Rating Scale [NRS] **[Appendix 3]** at T4-T7); frail scores (assessed by the Fatigue, Resistance, Ambulation, Illness and Loss of Weight Index [FRAIL] **[Appendix 4]** at T5-T8); and sleep quality score (assessed by the Pittsburgh Sleep Quality Index [PSQI] **[Appendix 5]** at T4-T8).

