## Appendix 1. The Hospital Anxiety and Depression Scale

### The Hospital Anxiety and Depression Scale

Name :

Date:

Doctors are aware that emotions play an important part in most illnesses.  
If your doctor knows about these feelings he will be able to help you more.

This questionnaire is designed to help your doctor to know how you feel.  
Ignore the numbers printed on the left of the questionnaire. Read each item  
and underline the reply that comes closest to how you have been feeling in the  
past week.

Don't take too long over your replies: your immediate reaction to each item  
will probably be more accurate than a long thought-out response.

| questions                                                                                  | answers                                | score |
|--------------------------------------------------------------------------------------------|----------------------------------------|-------|
| 01. I feel tense or 'wound up' (A):                                                        | Most of the time                       | 3     |
|                                                                                            | A lot of the time                      | 2     |
|                                                                                            | From time to time, occasionally        | 1     |
|                                                                                            | Not at all                             | 0     |
| 02. I still enjoy the things I used
to enjoy (D):                                       | Definitely as much                     | 0     |
|                                                                                            | Not quite so much                      | 1     |
|                                                                                            | Only a little                          | 2     |
|                                                                                            | Hardly at all                          | 3     |
| 03. I get a sort of frightened
feeling as if something awful is
about to happen (A): | Very definitely and quite badly        | 3     |
|                                                                                            | Yes, but not too badly                 | 2     |

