### Pittsburgh Sleep Quality Index

---

Name:

Date:

Instructions:

The following questions relate to your usual sleep habits during the past month only. Your answers should indicate the most accurate reply for the majority of days and nights in the past month.

Please answer all questions.

1. During the past month, when have you usually gone to bed at night?

USUAL BEDTIME:

2. During the past month, how long (in minutes) has it usually taken you to fall asleep each night?

NUMBER OF MINUTES :

3. During the past month, when have you usually gotten up in the morning?

USUAL GETTING UP TIME :

4. During the past month, how many hours of actual sleep did you get at night?  
(This may be different than the number of hours you spend in bed.)

HOURS OF SLEEP PER NIGHT :

For each of the remaining questions, check the best response. Please answer all questions.

5. During the past month, how often have you had trouble sleeping because you...

- (a) Cannot get to sleep within 30 minutes

Not during past month

The Less than Once a week

Once or twice a week

Three or more times a week

- (b) Wake up in the middle of the night or early morning

Not during past month

The Less than Once a week

Once or twice a week

Three or more times a week

- (c) Have to get up to use the bathroom

Not during past month

The Less than Once a week

---

|                      |                            |
|----------------------|----------------------------|
| Once or twice a week | Three or more times a week |
|----------------------|----------------------------|

(d) Cannot breathe comfortably

|                       |                            |
|-----------------------|----------------------------|
| Not during past month | The Less than Once a week  |
| Once or twice a week  | Three or more times a week |

(e) Cough or snore loudly

|                       |                            |
|-----------------------|----------------------------|
| Not during past month | The Less than Once a week  |
| Once or twice a week  | Three or more times a week |

(f) Feel too cold

|                       |                            |
|-----------------------|----------------------------|
| Not during past month | The Less than Once a week  |
| Once or twice a week  | Three or more times a week |

(g) Feel too hot

|                       |                            |
|-----------------------|----------------------------|
| Not during past month | The Less than Once a week  |

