| Once or twice a week  | Three or more times a week |

(h) Had bad dreams

|                       |                            |
|-----------------------|----------------------------|
| Not during past month | The Less than Once a week  |
| Once or twice a week  | Three or more times a week |

(i) Have pain

|                       |                            |
|-----------------------|----------------------------|
| Not during past month | The Less than Once a week  |
| Once or twice a week  | Three or more times a week |

(j) Other reason(s), please describe:

How often during the past month have you had trouble sleeping because of this?

|                       |                            |
|-----------------------|----------------------------|
| Not during past month | The Less than Once a week  |
| Once or twice a week  | Three or more times a week |

6. During the past month, how would you rate your sleep quality overall?

|           |             |            |          |
|-----------|-------------|------------|----------|
| Very good | Fairly good | Fairly bad | Very bad |
|-----------|-------------|------------|----------|

7. During the past month, how often have you taken medicine (prescribed or “over the counter”) to help you sleep?

|                       |                            |
|-----------------------|----------------------------|
| Not during past month | The Less than Once a week  |
| Once or twice a week  | Three or more times a week |

---

8. During the past month, how often have you had trouble staying awake while driving, eating meals, or engaging in social activity?

|                       |                            |
|-----------------------|----------------------------|
| Not during past month | The Less than Once a week  |
| Once or twice a week  | Three or more times a week |

9. During the past month, how much of a problem has it been for you to keep up enough enthusiasm to get things done?

|                            |                            |
|----------------------------|----------------------------|
| No problem at all          | Only a very slight problem |
| Only a very slight problem | A very big problem         |

10. Do you have a bed partner or roommate?

|                                        |                                |
|----------------------------------------|--------------------------------|
| No bed partner or roommate             | Partner/roommate in other room |

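### The PSQI covers the past month but is given at T4 to T7, so early scores describe almost only preoperative sleep; the past-week HADS-A has the same mismatch to an unknown degree

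*Protocol*

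**What the plan says.** **Sleep.** Protocol section III.J lists a "sleep quality score (assessed by the Pittsburgh Sleep Quality Index [PSQI"]) at T4 to T8: two hours after surgery, days 1, 2 and 3, and month 3. The form in Appendix 5 opens with "The following questions relate to your usual sleep habits during the past month only", and its questions repeat that period. Section III.G analyses secondary outcomes with a linear mixed model that has the T0 value as a covariate. Section III.J schedules no PSQI at T0.

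**Anxiety.** Section III.J states: "The primary outcome is the incidence of perioperative anxiety in patients from the day of surgery to 3 days after surgery after two sessions of" stimulation. It adds: "Perioperative anxiety was measured using the Hospital Anxiety and Depression Scale-Anxiety (HADS-A"), and "A HADS-A score of 8 or more is considered to be a patient experiencing anxiety". Anxiety is assessed on the day before surgery (T0), "followed by a second assessment of anxiety (T1) after the first tDCS intervention". It is assessed again on the day of surgery before (T2) and after (T3) session 2, two hours after surgery (T4), on days 1 to 3 (T5 to T7) and at month 3 (T8). The form in Appendix 1 tells patients to read each item "and underline the reply that comes closest to how you have been feeling in the" past week.

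The sessions fall on the day before and the day of surgery (section III.H). Nowhere does the protocol change either recall period for the short-interval assessments.

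**The concern.** A questionnaire can show a treatment effect only over the period it asks about. If most of that period lies before treatment, both arms report largely the same untreated time, and a real difference shrinks.

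For the PSQI, four of the five scheduled assessments fall within days of a treatment that the month-long window barely reaches. For HADS-A, the time points that make up the primary outcome fall within about three days of session 2, against a seven-day window. Baseline anxiety is not an exclusion criterion. A patient who was anxious before treatment and follows the form can therefore still reach the cut-off of 8 after a stimulation that worked.

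The forms and the schedule are fixed in the protocol. No later analysis can recover a period that the questionnaire did not ask about.

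**Working it through.** **Inputs from the protocol.** Sessions on day −1 and day 0 (III.H); assessment times (III.J); recall of 7 days for HADS (Appendix 1) and one month for PSQI (Appendix 5); 51.4% control incidence, 40% reduction, power 0.80, 88 per group, 10% loss (III.F); two-sided 0.05 (III.G).

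**Assumptions.** A month is 30 days; spacing is in whole days; T4 falls 0.25 to 0.5 day after session 2; T1 and T3 follow their sessions closely (the delay is not stated). The protocol does not list the primary time points by label; T3 to T7 is taken from its wording.

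**Share of the recall window after a session** = days since the session ÷ window length, capped at 100%.

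| Time | HADS week, from session 1 | HADS week, from session 2 | PSQI month, from session 1 | PSQI month, from session 2 |
|---|---|---|---|---|
| T1 | about 0% | – | – | – |
| T2 | 11–14% | – | – | – |
| T3 | 1/7 = 14% | about 0% | – | – |
| T4 | 18–21% | 4–7% | 4–5% | 1–2% |
| T5 | 2/7 = 29% | 1/7 = 14% | 2/30 = 7% | 1/30 = 3% |
| T6 | 3/7 = 43% | 2/7 = 29% | 3/30 = 10% | 2/30 = 7% |
| T7 | 4/7 = 57% | 3/7 = 43% | 4/30 = 13% | 3/30 = 10% |
| T8 | 100% | 100% | 100% | 100% |

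At T4 no postoperative night has yet passed. At T7 three have, out of about 30.

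**The plan's own sample size.** The 40% is read as relative: 0.514 × 0.6 = 0.3084. The pooled two-proportion formula without continuity correction gives 89 per group and the unpooled formula gives 86; power at 88 per group is 0.797. With loss, 88 ÷ 0.9 = 97.8, so 98. The stated 88 and 98 reproduce within rounding, so the problem is not arithmetic.

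**Illustration of dilution, 88 per group.** Suppose that patients weight the seven days equally, and that 51.4% versus 30.8% is the effect on current anxiety. With post-treatment share w:

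- Linear: p2 = 0.514 − w × 0.2056. For w = 4/7, p2 = 0.3965 and power is 0.35. For w = 3/7, p2 = 0.4259 and power is 0.21.
- Probit: the planned shift is 0.535 SD, multiplied by w. For w = 0.57, p2 = 0.394 and power is 0.36. For w = 0.43, p2 = 0.423 and power is 0.23.

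The two models agree closely, but both rest on the same two assumptions.

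**The case against.** **Patients may answer by how they feel now.** The HADS form asks for an immediate reaction rather than a considered one, and its items are in the present tense. Current state may dominate the replies. This stands: the size of the HADS-A dilution is unknown. It does not remove the mismatch, because the protocol then relies on patients departing from the printed period. It is weaker for the PSQI, whose form restricts the answer to the past month and repeats this throughout.

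**The planned effect may already be the effect on the measured score.** Section III.F speaks of the incidence of perioperative anxiety, the same term that defines the primary outcome. It does not say which instrument or recall period lay behind the preliminary 51.4%. This stands. A reader might infer from the illustration that the trial has power of 0.2 to 0.4; the document does not support that.

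**Not every assessment is mostly pre-treatment.** A reader might infer that all HADS-A assessments through T7 cover mainly the time before any stimulation. That holds through T6 only: at T7, 57% of the week follows session 1. The statement covers all of T3 to T7 only when counted from session 2, which the outcome's reference to two sessions supports. Nor does it follow that T1 can show no effect at all; that needs strict adherence to the form, and T1 lies outside the primary window.

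**The bias is towards no effect.** Both arms complete the same forms. This stands: the mismatch costs sensitivity and does not create a false positive.

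**Conclusion.** The point holds most firmly for the PSQI. At T4 to T7 only about 4% to 13% of the month follows any stimulation. If patients follow the form, these four scores measure almost only preoperative sleep and cannot answer whether tDCS changes postoperative sleep. T8 is unaffected. The model's T0 covariate is not available for PSQI under the stated schedule.

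For HADS-A the mismatch is real and reaches the primary outcome, but its effect cannot be sized from the protocol. Counted from session 2, the post-treatment share of the week runs from about 0% at T3 to 43% at T7, so a patient who follows the form reports mainly the time before treatment was complete. The likely direction is towards no effect. The power values are an illustration and do not show that the trial is underpowered. The shares rest on whole-day spacing and a 30-day month.

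A separate, minor matter: in PSQI question 9 one row pairs the no-problem answer with the very-slight one, and the next row reads "Only a very slight problem | A very big problem". The very-slight answer thus appears twice. Whether this is an error on the form or came from conversion of the document cannot be told from the text.

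**What to change.** **PSQI.** Give it at T0 and T8 only, and compare T8 between groups adjusted for T0. This supplies the missing baseline and reduces five administrations to two. The cost is that there is no PSQI score for the first days. If early sleep matters, use a single rating of last night's sleep on days 1 to 3.

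**HADS-A.** Reconcile the recall wording with the assessment times, in one of two ways:

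- State a shorter recall period, with the same wording at T0 and at every post-treatment assessment compared with it, and with reply options that fit. A changed header alone is not enough. Anxiety items 01, 05, 09 and 13 are answered by frequency, which needs a period and does not suit a question about this moment. Wording that differs from T0 would break the comparison with baseline in section III.G. The cut-off of 8 and the 51.4% behind the sample size would also need to be justified for the new recall period.
- Use a state-anxiety measure for the short intervals. This adds an instrument, and the primary outcome's definition would need to be reconsidered if it relied on that measure.

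In either case, do not read T0/T1 and T2/T3 differences on the past-week form as immediate effects.

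**PSQI question 9.** Check the repeated answer against the source form and correct it if the printed form carries it.

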|                                                                               | Usually                               | 1 |
|                                                                               | Not often                             | 2 |
|                                                                               | Not at all                            | 3 |
| 08. I feel as if I am slowed down (D):                                        | Nearly all the time                   | 3 |
|                                                                               | Very often                            | 2 |
|                                                                               | Sometimes                             | 1 |
|                                                                               | Not at all                            | 0 |
| 09. I get a sort of frightened feeling like 'butterflies' in the stomach (A): | Not at all                            | 3 |
|                                                                               | Occasionally                          | 2 |
|                                                                               | Quite often                           | 1 |
|                                                                               | Very often                            | 0 |
| 10. I have lost interest in my appearance (D):                                | Definitely                            | 0 |
|                                                                               | I don't take so much care as I should | 1 |
|                                                                               | I may not take quite as much care     | 2 |
|                                                                               | I take just as much care as ever      | 3 |
| 11. I feel restless as if I have to be on the move (A):                       | Very much indeed                      | 3 |
|                                                                               | Quite a lot                           | 2 |
|                                                                               | Not very much                         | 1 |
|                                                                               | Not at all                            | 0 |

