| 12. I look forward with enjoyment to things (D):                              | As much as ever I did                 | 3 |
|                                                                               | Rather less than I used to            | 2 |
|                                                                               | Definitely less than I used to        | 1 |
|                                                                               | Hardly at all                         | 0 |
| 13. I get sudden feelings of panic (A):                                       | Very often indeed                     | 0 |
|                                                                               | Quite often                           | 1 |
|                                                                               | Not very often                        | 2 |
|                                                                               | Not at all                            | 3 |
| 14. I can enjoy a good book or radio or TV programme (D):                     | Often                                 | 0 |
|                                                                               | Sometimes                             | 1 |
|                                                                               | Not often                             | 2 |
|                                                                               | Very seldom                           | 3 |

"(A)" scores were used to screen for the presence of anxiety symptoms;

A: \_\_\_\_\_

8~10: mild anxiety, 11~14: moderate anxiety, 15~21: severe anxiety

---

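### Appendix 1 scores two of the seven HADS-A items (09 and 13) in the opposite direction to the other five, so the primary outcome is misclassified if totals were computed with the printed key

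*Protocol*

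**What the plan says.** Protocol section J (Outcome measures) defines the endpoint: "The primary outcome is the incidence of perioperative anxiety in patients from the day of surgery to 3 days after surgery". It names the HADS anxiety subscale as the instrument, refers to Appendix 1 for it, and sets the threshold: "A HADS-A score of 8 or more is considered to be a patient experiencing anxiety". The HADS-A scores at T1 to T8 are also a secondary outcome.

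Appendix 1 prints each reply with its score. The items marked (A) are 01, 03, 05, 07, 09, 11 and 13, each scored 0 to 3, and the (A) total is read as "8~10: mild anxiety, 11~14: moderate anxiety, 15~21: severe anxiety". A high total therefore means more anxiety.

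- Items 01, 03, 05, 07 and 11 follow that direction. In item 03, for example, "Very definitely and quite badly" scores 3 and *Not at all* scores 0.
- Item 09 does not: "09. I get a sort of frightened feeling like 'butterflies' in the stomach (A): | Not at all" carries 3, then *Occasionally* 2, *Quite often* 1, *Very often* 0.
- Item 13, "13. I get sudden feelings of panic (A"), does not either: *Very often indeed* carries 0, *Quite often* 1, *Not very often* 2, *Not at all* 3.

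The protocol gives no recoding rule and no other scoring key.

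**The concern.** Two of the seven items contradict both the other five and the severity bands on the same form. Items 03 and 09 show it most plainly: both ask about a frightened feeling, yet *Not at all* scores 0 in one and 3 in the other.

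This key feeds the primary outcome. Under it, a treatment that reduces panic and fright raises the score on items 09 and 13, against its effect on the other five. At stake are the classification of patients at the cut-off of 8, the relative risk (RR), the power of the primary test and the anxiety scores at T1 to T8.

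**Working it through.** **1. The plan's own sample size.** Inputs from section F: control incidence 51.4%, 40% relative reduction, power 0.80, alpha 0.05 (two-sided in section G), 10% loss. The active-arm incidence is 0.514 × 0.60 = 0.3084, so RR = 0.60 and the difference is 20.6 points. The usual two-proportion formula gives 89 per group with pooled variance and 86 with unpooled variance. Power at 88 per group is 0.797, and 88 / 0.90 = 97.8, rounded up to 98. The stated 88 and 98 are reproduced, so the sample size is not at fault.

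**2. What the printed key does (exact).** Let A be the correctly directed sum of items 01, 03, 05, 07 and 11 (0 to 15), and B the correctly directed sum of items 09 and 13 (0 to 6).

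- Consistent score = A + B.
- Printed score = A + (6 − B).

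| Patient | A | B | Consistent score | Printed score |
|---|---|---|---|---|
| No symptom on any item | 0 | 0 | 0 | 6 |
| Worst reply on all seven | 15 | 6 | 21 | 15 |
| Two points on the five items, none on 09 and 13 | 2 | 0 | 2 | 8 (anxious) |
| Seven points on the five items, worst reply on 09 and 13 | 7 | 6 | 13 | 7 (not anxious) |

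A printed score of 8 or more means A − B ≥ 2, whereas the intended rule is A + B ≥ 8. Errors go both ways. A printed total of 21 needs a patient with no butterflies and no panic.

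**3. Mean score.** If treatment shifts every item by the same amount, the printed difference keeps (5 − 2) / 7 = 43% of the true one. This concerns the T1 to T8 scores and does not measure the loss on the binary endpoint.

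**4. Binary endpoint (by simulation, on assumptions).** The protocol has no item-level data. Seven correlated 0-to-3 items were simulated, with the correctly scored incidence set to 51.4% versus 30.84%. The assumptions varied were the latent correlation between items (0.3, 0.5, 0.7), the spacing of the reply thresholds (single-assessment model), and whether items 09 and 13 are endorsed as often as the others or less often. The endpoint was either one assessment or a score of 8 or more at any of five assessments.

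| Printed key | Sham | Active | Difference (points) | RR | Power, 88 per group |
|---|---|---|---|---|---|
| One assessment | 70–93% | 52–85% | 7–18 | 0.74–0.92 | 0.33–0.68 |
| Any of five | 83–99% | 68–96% | 3–16 | 0.81–0.97 | 0.21–0.69 |
| Plan, consistent key | 51.4% | 30.8% | 20.6 | 0.60 | 0.80 |

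In the single-assessment runs, 32–85% of patients who are not anxious on the consistent key are classed as anxious, and 0–11% of anxious patients are missed. Every run showed attenuation and lost power.

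**The case against.** **The key may be a misprint that never touched the data.** No section says that totals are computed from the printed score column, or that this English page is what patients complete. The form tells patients to ignore numbers on its left, but the scores stand on the right. That hints at a retyped copy without proving it, since the left-hand numbers could be the item numbers. If data entry used a consistent key, outcome, RR and power are untouched. This stands: the harm is conditional. The contradiction itself is not, and this is the only key the protocol supplies.

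**A table-reading error.** This is unlikely. Each score sits in the row of its own reply, and the reversed items run in unbroken order.

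**A reader might infer that the treatment effect is largely cancelled.** The documents do not support that. Across the runs the risk difference is about 2.8 to 17.8 points, so between 2.8 / 20.6 = 14% and 17.8 / 20.6 = 86% of the planned difference remains. Attenuation with loss of power is what can be said.

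**A reader might also infer that the 51.4% no longer fits the trial.** That would require the preliminary data to have been scored with a different key, and section F does not say how they were scored. If the same key was used for both, this mismatch does not arise, although the 51.4% would then itself need re-scoring.

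**Conclusion.** The point holds. Appendix 1 is wrong as written: items 09 and 13 contradict the other five anxiety items and the form's own bands, and following the printed key gives a wrong primary outcome. The totals of 6 for no symptoms and 15 for the worst replies follow exactly from the form.

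The effect on the trial is conditional on totals having been computed with that key. If they were, misclassification is mainly false-positive, the T1 to T8 anxiety scores are distorted, the RR moves from 0.60 to about 0.74–0.97, and power at 88 per group falls from 0.80 to about 0.2–0.7. These ranges rest on assumed item correlations, thresholds and endorsement, on one or five assessments, and on 51.4% and 30.8% being the incidences under a consistent key. They show direction and plausible size and are not estimates for this trial. That the outcome was in fact misclassified is not shown by the protocol.

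Two side matters do not add to the weight of this point. Depression items 10 and 12 are also reversed, but they do not enter HADS-A and no depression outcome is listed. PSQI item 9 repeats a reply option ("Only a very slight problem | A very big problem" follows a row that already ends with the slight-problem option). A reader might infer that the item cannot be scored, but its four options stand in sequence and Appendix 5 prints no scoring key, so that is not shown.

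**What to change.** 1. Correct Appendix 1. Item 09: *Not at all* 0, *Occasionally* 1, *Quite often* 2, *Very often* 3. Item 13: *Very often indeed* 3, *Quite often* 2, *Not very often* 1, *Not at all* 0.
2. State in writing which key was used to total the trial forms and the preliminary data behind the 51.4%.
3. Re-score from item-level replies anything totalled with the printed key, and compute HADS-A by program from the items. If the 51.4% changes, revisit section F.
4. On the same occasion, correct the direction of depression items 10 and 12 and the repeated reply option in PSQI item 9.

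The cost is a corrected form, a scoring program and, if needed, re-scoring from stored replies. No extra patients or visits are required. Re-scoring is possible only if item-level replies were kept, so that should be checked first.
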